# Training and Assessing Teamwork in Interprofessional Virtual Reality–Based Simulation Using the TeamSTEPPS Framework: Protocol for Randomized Pre-Post Intervention Study

**DOI:** 10.2196/68705

**Published:** 2025-05-27

**Keywords:** interprofessional teamwork, medical education, TeamSTEPPS, Team Performance Observation Tool, team training, Teamwork Perceptions Questionnaire, virtual reality

## Abstract

**Background:**

Interprofessional teamwork is essential for patient outcomes in emergency medicine; yet, effective training in this area is scarce. Virtual reality (VR) provides a promising, resource-efficient solution for simulating emergency scenarios and facilitating interprofessional collaboration. While VR-based training has shown benefits for medical skill and knowledge acquisition, assessing teamwork within such environments remains a challenge due to the lack of validated measurement tools. Existing teamwork assessment instruments, developed for physical simulations, may not fully apply to VR due to differences in communication modalities, interaction mechanics, and observer perspectives.

**Objective:**

This study aims to adapt and validate the TeamSTEPPS framework to assess teamwork in VR-based training. Subsequently, these adapted instruments will enable the investigation of whether interprofessional teamwork can be successfully trained in VR scenarios.

**Methods:**

Prior to the study, measurement instruments for subjective (Teamwork Perceptions Questionnaire) and objective teamwork quality (Team Performance Observation Tool, TPOT) will be adapted and validated for use in VR scenarios. Validation of the adapted version of the Team Performance Observation Tool includes expert consensus via a modified Delphi method as well as validity and reliability testing using recorded VR teamwork sessions. The study itself is designed as a prospective pre-post study with a planned enrollment of 65 nursing and 65 medical students working in randomly assigned interprofessional teams. On 3 timepoints (day 1, day 8, and day 15), participants engage in a VR scenario simulating 1 out of 3 different emergency medical conditions (esophageal variceal bleeding, exacerbated chronic obstructive pulmonary disease, and atrial fibrillation due to urinary tract infection). As an intervention, a structured training video on successful teamwork according to the TeamSTEPPS concept is shown on day 8 immediately before the second VR scenario. Teamwork is assessed objectively with the adapted version of the Team Performance Observation Tool and subjectively with the adapted Teamwork Perceptions Questionnaire. Medical performance will be recorded automatically by the VR software based on the medical measures conducted by the team.

**Results:**

As of May 2024, a total of 28 interprofessional teams have been enrolled. Data analysis will begin in late 2025.

**Conclusions:**

This study addresses the challenge of adapting teamwork assessment tools to VR environments and may provide insights into the potential of VR-based training for improving interprofessional collaboration in medical education. Future research could include a control group to measure the effects of team training more rigorously or use more enhanced technologies (eg, natural language processing) to capture the full range of teamwork behavior.

**International Registered Report Identifier (IRRID):**

DERR1-10.2196/68705

## Introduction

Interprofessional teamwork plays a crucial role in affecting patient outcomes in emergency medical contexts [1,2]. However, interprofessional team training is uncommon both in undergraduate medical education and in professional practice [3,4]. This is particularly due to the high personnel and resource requirements for effective team training [5,6]. Virtual reality (VR)–based training environments are playing an increasing role in emergency medicine, facilitating the widespread and effective learning of medical content, and may also enable interprofessional team collaboration training in the future [7]. The improvement in medical performance through such training is measured using various parameters such as checklists or “time to action” [8-11]. Some VR programs already allow for automated result recording [10], which could support examiners in complex practical examination settings in the future.

In contrast to capturing medical knowledge or performance, there are currently no validated tools for measuring (interprofessional) team collaboration in VR-based environments. For conventional physical simulation–based training, numerous tools exist to objectively capture various aspects of teamwork [12,13]. These are often based on Crew Resource Management or similar principles. However, these evaluation criteria cannot be fully transferred to VR scenarios for several reasons: Currently, team-capable VR training environments vary significantly in their level of functionality. For instance, considerable differences exist in how verbal interaction with virtual patients is represented (either through menu-based options or speech recognition [14]) and how haptic measures are depicted (solely via VR controllers [15,16] or additional haptic devices [8]). The ways teamwork is represented in VR environments (verbal communication, handing over objects, as well as briefing and debriefing) also may differ and nonverbal communication skills such as facial expressions and nuanced gestures are largely missing among current VR-based avatars. Finally, it is crucial to provide evaluators with a sufficient view of the actions and verbal communication in the VR scenario—whether as participants wearing a VR headset or through visualizing the participants’ perspectives on a computer screen. These challenges may explain why the quality of teamwork in VR-based environments has barely been measured so far. While technical hurdles are increasingly being overcome through advances in hardware and software, assessment tools for team collaboration in virtual settings still need to be adapted and validated.

A well-validated framework that includes educational content and both subjective and objective tools for assessing teamwork in physical simulations is the TeamSTEPPS framework [17]. In its current version (3.0), it covers 5 dimensions: team structure, communication, leadership, situation monitoring, and mutual support, and provides both subjective and objective evaluation metrics. The objective metric, the Team Performance Observation Tool (TPOT), has been significantly enhanced in terms of test-retest and interrater reliability through the inclusion of behavioral anchors compared to the original version [18]. In a recently published comparison of the most promising team performance assessment tools for evaluating longitudinal training, the TPOT was rated the most comprehensive tool and showed the second-best interrater reliability [19]. The associated questionnaire for subjective team member perceptions, the Teamwork Perceptions Questionnaire (T-TPQ), is also well-researched and validated [20]. While other assessment tools may outperform in specific criteria [12], the TeamSTEPPS concept is well suited for studies assessing comprehensive learning outcomes in simulations due to its alignment between teaching and assessment tools.

This study aims to adapt and validate objective and subjective assessment tools for the facets of teamwork that meet the requirements of VR-based environments, using the TeamSTEPPS measurement instruments. In the planned prospective study, these assessment tools will be used to measure the objective quality and the subjective perceptions of teamwork longitudinally (before, immediately after, and 1 week after completing a VR-based team training). In addition, the medical performance of the teams will be assessed based on the medical actions taken. The hypotheses derived from this are as follows:

H1: A VR-adapted TPOT (vTPOT) supplemented with behavioral anchors demonstrates good item characteristics (concurrent validity, interrater reliability, and internal consistency) for the various facets of teamwork compared to the original version.H2: VR-based team training leads to a sustainable objective improvement in all facets of teamwork performance in interprofessional teams (as measured with the vTPOT).H3: VR-based team training leads to sustainable subjective improvement in all facets of teamwork perceptions in interprofessional teams (as measured with an adapted T-TPQ).H4: The increasing quality of teamwork is associated with an improvement in treatment quality, represented by the automatically recorded percentage of correctly performed medical actions.

## Methods

### Apparatus

STEP-VR (version 1.0; ThreeDee GmbH, Munich, Germany) will be used as the VR simulation of complex emergencies, which represents a joint development between a 3D visualization company and the University Hospital of Würzburg. The version includes multiuser functionality, allowing the selection of an avatar with typical nursing or medical attire and multiple stylized faces (Figure 1).

The VR hardware setup for this study includes 2 OMEN by HP 17-ck0075ng Laptops (chipset: Intel Core i7-11800H; graphics adapter: NVIDIA GeForce RTX 3070 Laptop GPU [8 GB GDDR6 dedicated]) and 2 Oculus Quest III VR head-mounted displays (HMDs). The equipment enables STEP-VR to run at a constant framerate of over 60 frames per second on “high quality” display settings of the HMD.

**Figure 1 figure1:**
[figure not shown]
Top left: participants with the virtual reality head-mounted display and image transmission to a monitor (background) for the study staff. Top right: interaction of stylized avatars in the first-person perspective. Bottom left: final evaluation after the simulation with an assessment of medical performance. Bottom right: overview showing stylized avatars and a virtual patient.

#### Adaptation and Validation of the T-TPQ for VR-Based Scenarios

The 35-item self-report tool T-TPQ developed by TeamSTEPPS, uses 5-point Likert scales to measure staff perceptions of Team Structure, Team Leadership, Situation Monitoring, Mutual Support, and Communication. These 5 facets of teamwork correspond to those described in the above-mentioned TPOT. The 5-point Likert scale ranges from 5=“strongly agree” to 1=“strongly disagree.” All items of the T-TPQ were translated into German.

For the identification of inappropriate items of the T-TPQ, quantitative and qualitative methods will be applied. In the first step, as part of a pilot study, all participants initially answered the 35 items of the original T-TPQ. Following this, internal consistency is calculated and items that strongly deviate from the responses to other items will be identified.

In the second step, an additional response option, “not applicable,” will be integrated into the T-TPQ for all items. Also, within the pilot study, participants will be asked to explain why they had rated an item as “not applicable.” Exclusion of inappropriate items will be made based on these analyses.

### Study Design

A prospective preintervention-postintervention study will be conducted between May 2024 and June 2025. Teams consisting of 1 nursing and 1 medical student will complete 3 different interprofessional VR-based scenarios on 3 dates. These teams will be newly randomized for each session.

Three scenarios, each lasting about 30 minutes, will be completed by all participants in random order on different dates: (1) esophageal variceal bleeding due to ethyl-toxic liver cirrhosis, (2) exacerbated chronic obstructive pulmonary disease, and (3) tachycardic atrial fibrillation due to complicated urinary tract infection. The contents of the scenarios and indicated medical actions are listed in Table S1 in Multimedia Appendix 1 and were already described in detail elsewhere [16,22]. Participants can communicate via voice-over IP and interact with each other through avatars during the scenarios (eg, handing over equipment or demonstrating findings on a screen). The type and order of medical actions and teamwork elements are not predetermined and can be independently structured by the team members (eg, briefing and mid-discussion). After the scenario, a detailed guideline-based evaluation of the medical actions and an overview of the physiological course of the disease can serve as the basis for debriefing.

On the first date (day 1), informed consent will be obtained. A tutorial will follow to familiarize participants with VR hardware and software. The first scenario will be completed without specific prior team training (pre-test). On the second date (day 8), a training video on successful teamwork including practical recommendations will be shown (approximately 30 min). The content of the training video is based on the official TeamSTEPPS guidelines [17] and has been adapted by the authors of the study to fit the specific context (limited time and VR setting). In addition, video examples were shown to demonstrate how certain team interactions (particularly for performing “Check-Backs,” “Huddles,” giving feedback, and applying the “Two-Challenge Rule”) can be implemented in VR. Then, the second scenario will be completed (post test). A total of 7 days later (day 15), without additional training, the third and final scenario will be completed (retention test). Figure 2 provides an overview of the study design and data collection.

**Figure 2 figure2:**
[figure not shown]
Overview of the data collection process. vTPOT: Team performance observation tool adapted for virtual reality scenarios. T-TPQ: TeamSTEPPS T-TPQ; VR: virtual reality.

### Participants

#### Overview

All regularly enrolled nursing students in their second-third year of training and all medical students in their 8th-10th semester at the University Hospital of Würzburg are eligible to participate. Participants of the study will provide written informed consent after being detailed on the study conditions. Inclusion criteria and exclusion criteria are listed in Textbox 1.

Eligibility criteria.
**Inclusion criteria**
Regularly enrolled nursing students in their second or third year of training or medical students in their eighth to tenth semesterSigned informed consent provided18 years of age
**Exclusion criteria**
Known epilepsyKnown severe motion sickness

#### Sample Size Calculation

Since the team tandems are reassembled in a new, randomized form at each session a sample size estimation for 3 repeated measures timepoints could not be computed. Instead, we had to assume 3 independent groups. A between-groups ANOVA with an α level of 5%, a power of 80%, and assuming a large effect size, indicated that approximately 65 team tandems would be required, resulting in a total of 130 participants.

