### Statistical Analysis

Test quality criteria of vTPOT will be assessed as follows: For concurrent validity, Pearson correlations will be calculated. Interrater reliability of the vTPOT will be calculated using Cohen Kappa to quantify the agreement between the assessments of the independent reviewers. Internal consistency of the vTPOT will be assessed by using Cronbach α. A value exceeding 0.7 will be considered acceptable, and greater than 0.8 as good. Considering the results of objective team performance, subjective teamwork perception, medical performance scores, and descriptive statistics including mean and SD will be calculated and presented in the format of mean and SD. Pearson correlations will be calculated to capture relationships between the results of different measurement instruments. The Shapiro-Wilk test is used to check for normal distribution. In case of a violation of the normality assumption, nonparametric tests (Wilcoxon rank test for group differences and Spearman test for correlations) are used. The calculations and generation of figures will be performed using GraphPad Prism (Version 10.1.2; GraphPad Software Inc).

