Despite these strengths, there are several limitations to consider. First, the absence of a control group limits our ability to definitively attribute improvements in teamwork to the VR-based training intervention alone. The pre-post design allows for intragroup comparisons, but the lack of a parallel group experiencing conventional training or no training reduces the robustness of our findings. In particular, regarding the subjectively perceived quality of teamwork, an anticipated treatment effect of uncertain magnitude could arise due to the lack of a control group. To mitigate this, we reassemble the teams for each session. While an effect due to mere repetition is also conceivable for the objective measurements of teamwork quality, it is less likely, as most TeamSTEPPS concepts (eg, check-backs, the Two-Challenge Rule) are unlikely to be learned intuitively. Moreover, the intervention (the training video on successful teamwork) is significantly shorter than typical training sessions from the TeamSTEPPS framework and may not achieve a sufficient effect. However, with regard to future application, it seemed important to find a training concept that could be applied both in academic studies and within the tightly scheduled clinical routine. In addition, the study is conducted at a single institution, which may restrict the generalizability of the results to other educational contexts or healthcare systems. Finally, another limitation stems from the voluntary nature of participant enrollment. It is possible that those opting to participate may already have a positive attitude toward teamwork or technology, potentially introducing a selection bias.

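### Re-forming the teams does not make the three sessions independent groups or rule out a repeated-measures calculation, and no test the article names for the team scores fits the crossed design

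*Protocol article*

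**What the plan says.** - **Sample Size Calculation.** Because tandems are newly drawn for each session, "a sample size estimation for 3 repeated measures timepoints could not be computed". The article continues: "Instead, we had to assume 3 independent groups". The number comes from a between-groups ANOVA at 5% alpha with "a power of 80%, and assuming a large effect size", giving about 65 tandems (130 participants).
- **Study Design.** "Three scenarios, each lasting about 30 minutes, will be completed by all participants in random order on different dates". Partners are re-randomised each time.
- **Statistical Analysis.** Means and SDs, Pearson correlations and a Shapiro-Wilk check are planned. If normality fails, "nonparametric tests (Wilcoxon rank test for group differences and Spearman test for correlations) are used". No parametric test of differences between sessions is named here, and the section does not say whether the Wilcoxon test is rank-sum or signed-rank.
- **Measures of Teamwork Quality.** T-TPQ is completed by individuals after the first and third scenarios only. Under Ethical Considerations, questionnaires are collected anonymously.
- **Strengths and Limitations.** "The pre-post design allows for intragroup comparisons".

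**The concern.** Every student contributes to a tandem score on day 1, day 8 and day 15. Re-pairing changes who is combined with whom; it does not replace the people. The scores are therefore cross-classified by nursing student and medical student. That differs from a simple repeated measure on fixed teams, and it also differs from three independent samples. The Discussion treats the comparison as within-group, which does not agree with the sample-size premise.

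The one three-session test in the article rests on that premise. The Wilcoxon fallback does not fill the gap for team scores. As a rank-sum test it ignores that the students recur; as a signed-rank test it needs teams that persist, and none do. H2 claims improvement that lasts, over three dates, so the choice of test matters. At stake are the precision of the H2 estimates and, for H3, the false-positive rate under one plausible reading.

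**Working it through.** The article gives no value for the effect size, for the variance due to students or for the scenario differences. The values below are assumptions, shown as ranges.

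**1. The article's own figure.** One-way ANOVA, k = 3, noncentrality N·f², df (2, N − 3), alpha 0.05, power 0.80. Reading large as f = 0.40 gives N = 64 in total, or 66 if balanced (22 per session); power at N = 65 is 0.81. So 65 reproduces as the total over three groups. The design plans 65 tandems at each session, 3 × 65 = 195 scores, where the same formula gives over 99.9% power at f = 0.40 and 80% power at f ≈ 0.22. With the 28 teams enrolled by March 2025 (84 scores), power is 91% at f = 0.40.

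**2. What independence does to vTPOT.** Write score = session + nursing-student effect + medical-student effect + residual, with total variance 1. Let ρ be the share due to the two student effects together. With full attendance each student enters every session mean once, so these effects cancel from a difference between sessions:

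- true variance of the difference = 2(1 − ρ)/n
- variance used by the independent-groups ANOVA = 2/n
- ratio of SEs = 1/√(1 − ρ)

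For n = 65 the ANOVA uses √(2/65) = 0.175 SD. At ρ = 0.4 the true SE is √(1.2/65) = 0.136.

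Under no change, the ANOVA's rejection rate is approximately exp(−F_crit/(1 − ρ)), with F_crit(2, 192) = 3.04. Simulation with re-drawn partners agrees closely.

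| ρ | SE too wide by | type I error, formula (n = 65) |
|---|---|---|
| 0.2 | 12% | 2.2% |
| 0.3 | 20% | 1.3% |
| 0.4 | 29% | 0.6% |
| 0.5 | 41% | 0.2% |

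Simulated type I error at 65 tandems was 2.2–2.6% at ρ = 0.2 and 0.2–0.3% at ρ = 0.5. At 28 tandems it was about 2% and 0.2–0.4%.

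**3. Power.** The comparison is with a model that includes both student effects and session; its simulated type I error was 4–6%. There were 1,500 runs per setting at 65 tandems and 3,000 at 28.

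| setting | ρ | independent ANOVA | crossed model |
|---|---|---|---|
| 65 tandems, f = 0.20 | 0.2 | 71% | 79% |
| | 0.4 | 72% | 90% |
| | 0.5 | 72% | 94% |
| 28 tandems, 0.5 SD gain held at both later sessions (f = 0.5·√(2/9) = 0.24) | 0.2 | 44% | 53% |
| | 0.3 | 42% | 58% |
| | 0.5 | 39% | 73% |

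At f = 0.40 and 28 tandems, the ANOVA keeps 91–96% power over ρ = 0 to 0.5. This also shows that the calculation reported as impossible can be done.

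**4. T-TPQ.** Let r be the variance share of the person and c the share of the team-session that two partners have in common.

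- Paired by participant, team-session ignored: variance is understated by the factor 1 + c/(1 − r). With c = 0.3 and r = 0.2, 0.3, 0.5 the factors are 1.375, 1.429 and 1.600. Type I error is 2(1 − Φ(1.96/√factor)) = 9.5%, 10.1%, 12.1%.
- Unpaired: the factor is 1 + c − r. With c = 0.3 and r = 0, 0.3, 0.5 it is 1.3, 1.0 and 0.8, giving 8.6%, 5.0%, 2.8%.

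**5. Scenario.** With ρ = 0.4, 65 tandems and scenarios drawn in random order, leaving scenario out raises the SE of a session contrast from 0.137 to 0.142 (adjacent scenarios 0.25 SD apart) or from 0.136 to 0.163 (0.5 SD apart). The session estimate stays unbiased.

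**The case against.** - **The premise sits in the sample-size section.** The Statistical Analysis section never says sessions will be analysed as independent, and the Discussion speaks of intragroup comparisons. A reader might infer that the reported results will certainly carry wrong standard errors. The article does not support that; the vTPOT figures hold only if the ANOVA is carried over. What stands is that the stated reason is incorrect and that no other three-session test is printed.
- **The error is conservative for H2.** One might infer false claims of improvement, or a trial too small for its aim. Neither follows: type I error is below 5%, and power for a large effect is ample at 65 tandems per session and about 91% at 28. The figure of 28 is also an interim count during recruitment, not the plan.
- **Signed-rank can suit T-TPQ.** There are two time points per person, so pairing is natural if the forms can be linked. This is right as far as pairing goes, but it leaves the correlation between partners in the same session unaddressed. An unpaired test can err in either direction.
- **Scenario terms and model detail may sit in an analysis plan not shown.** This is fair. Because scenario order is random, omission costs precision and does not bias the session effect, so it would not be a finding by itself.
- **The student share of variance is unknown.** At ρ = 0.2 the SEs are only about 12% too wide.

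**Conclusion.** The point holds as a stated method that does not match the stated design. The claim that a repeated-measures calculation was impossible is wrong, and the independence premise conflicts with the Study Design and Discussion sections. The tests named do not give a three-session analysis of team scores that uses the recurrence of students.

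If the between-groups ANOVA is used for H2, the result is lost efficiency: SEs about 12–41% too wide and type I error of about 2% down to 0.3%, for an assumed student share of 20–50%. That matters for effects smaller than the large one assumed, and the authors themselves concede that the short video may not achieve a sufficient effect. For H3 the risk can run the other way: about 9–12% type I error for a participant-paired test that ignores the shared session, at an assumed within-team correlation of 0.3 and a person share of 20–50%. All correlations are assumptions, and full attendance is assumed throughout.

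**What to change.** Settle this before analysis starts, which the Abstract puts in late 2025.

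- **vTPOT and medical performance score:** fit a linear mixed model on team-sessions with session (day 1, 8, 15) and scenario as fixed effects and crossed random intercepts for the nursing and the medical student. Pre-specify two contrasts, day 8 vs day 1 and day 15 vs day 1, which answer improvement and retention directly.
- **T-TPQ:** use participant-level data with a team-session effect, and add a participant effect if the anonymous forms can be linked by a pseudonymous code.
- **Wilcoxon:** if it is kept, say which version, for which outcome and for which comparison.
- **Sample size:** delete the statement that the calculation could not be done. Restate the basis, for example by simulation with a numerical effect size and an assumed student share, and say whether 65 is a total or a per-session number.

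Cost: probably a change from the named GraphPad package to software that fits crossed random effects, and a little more analyst time. The vTPOT and medical-score models need no new data. The participant effect for T-TPQ depends on linkage that the article does not describe and that may not be recoverable for forms already collected. The scenario term is a gain in precision, not a correction of bias.

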## Results

This study received ethics approval in April 2024. As of May 2024, the enrollment of participants is ongoing and currently (March 2025) has 28 enrolled interprofessional teams. Data collection and analysis will be complete in December 2025.

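### The 65 tandems match the total over three independent groups, but the trial plans 65 at every session, so the stated size, 80% power and large effect do not agree

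*Protocol article*

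**What the plan says.** The Sample Size Calculation explains that a repeated-measures calculation was not possible because pairs are re-formed at each session, and continues: "Instead, we had to assume 3 independent groups". It then reports that a between-groups ANOVA at 5% alpha and 80% power, "assuming a large effect size, indicated that approximately 65 team tandems would be required, resulting in a total of 130 participants". The size of the large effect is not given as a number.

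The Abstract (Methods) gives a "planned enrollment of 65 nursing and 65 medical students working in randomly assigned interprofessional teams". The Study Design section says that the three scenarios "will be completed by all participants in random order on different dates", in pairs of one nursing and one medical student that are newly randomised each time.

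The Results section reports that the study "currently (March 2025) has 28 enrolled interprofessional teams".

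**The concern.** A one-way ANOVA calculation can be reported as a total or as a number per group, and with three groups the two differ by a factor of three. The conversion used here, 65 tandems times 2 people = 130 participants, is right for a total of 65 only if each student joins one tandem once. The trial has every student attend all three sessions, so 130 students form 65 tandems at each session. If the software returned 65 as the total, the trial's only sample-size justification describes a different number of observations from the one planned.

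The justification sets the target against which recruitment is judged, and it tells readers which effects the study was built to detect. With 28 teams reported in March 2025 against a target of 65, both uses are likely to matter when the results are written up.

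**Working it through.** **Inputs.** From the Sample Size Calculation: k = 3 groups, alpha = 0.05, power = 0.80, one-way between-groups ANOVA. From the Abstract and Study Design: 65 nursing and 65 medical students, pairs of one each, three sessions attended by all. Assumed: large means f = 0.40, with other values shown below. No dropout allowance is stated, and none is used.

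**Formula.** Power = P(F′ > F_crit), where F′ is noncentral F with df1 = k − 1 = 2, df2 = N − 3 and noncentrality λ = N·f². F_crit is the 95th percentile of the central F with the same degrees of freedom. N is the total number of observations over the three groups.

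**Step 1: reproduce the plan's figure, with f = 0.40.**

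| Total N | λ = 0.16·N | F_crit | Power |
|---|---|---|---|
| 63 | 10.08 | 3.150 | 79.8% |
| 64 | 10.24 | 3.148 | 80.5% |
| 65 | 10.40 | 3.145 | 81.2% |
| 66 | 10.56 | 3.143 | 81.8% |

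The smallest total reaching 80% is 64, and the smallest balanced total is 66 (22 per group). The stated figure of about 65 is therefore reproduced as a total.

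**Step 2: count what the trial will observe.** 130 students in pairs form 65 tandems per session, and 65 × 3 sessions = 195 team-sessions.

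**Step 3: apply the same calculation to N = 195 (F_crit = 3.043).**

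- f = 0.40: λ = 195 × 0.16 = 31.2, power 99.9%.
- f = 0.25 (conventionally medium): λ = 195 × 0.0625 = 12.19, power 88.3%.
- Solving for 80% power gives f = 0.224 (λ = 9.79).

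**Step 4: does the result depend on f = 0.40?** Total N needed for 80% power:

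| f | Total N |
|---|---|
| 0.25 | 158 |
| 0.35 | 82 |
| 0.40 | 64 |
| 0.50 | 42 |

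None of these comes to 195. Other readings at f = 0.40 do not either: two groups need 52 in total, 90% power needs 83, alpha of 0.05/3 needs 83 and alpha of 0.05/5 needs 92. A two-mean comparison needs 25 per group for d = 0.8. It needs 63 per group for d = 0.5, but that is a medium effect and not the ANOVA described.

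**Step 5: a smaller achieved number.** If 28 tandems completed all three sessions, N = 28 × 3 = 84. Power is then 90.7% at f = 0.40 and 50.9% at f = 0.25, and 80% power is reached at f = 0.345.

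**The case against.** The strongest reply is that the error is harmless. Under the plan's own independence assumption it calls for more teams than the inputs need. It changes no endpoint, procedure or test, and the planned number may stay as it is. This stands, and it limits the point to a correction of the stated rationale.

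A second reply is that the document never gives a value for the large effect, so reading 65 as a total is an inference. That is true. But f = 0.40 reproduces the figure, and no value that could be called large gives 65 per session at 80% power.

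A third reply is that all these figures rest on independence, which the article adopts only as a fallback. The same students recur in all three sessions, so 99.9% and f of about 0.22 are nominal. This also stands, and the corrected text should say so.

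Two stronger readings are tempting, and the document supports neither:

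- A reader might infer that with 28 teams enrolled (84 team-sessions) the trial has already passed its own requirement. The Results section speaks of enrolled teams and does not say how many completed three sessions. Because pairs are re-formed each time, 28 could even be a count of team-sessions.
- A reader might infer that 22 tandems (44 students) would be enough. That takes the independence approximation at face value and counts one omnibus test of one score, whereas the second hypothesis (H2) concerns all facets of teamwork and a sustained improvement.

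**Conclusion.** The sample-size statement is wrong as written and should be corrected. The figure of 65 fits 80% power and a large effect only as a total over three sessions, while the trial plans 65 at each, three times as many observations. At the planned size, nominal power for f = 0.40 is 99.9% rather than 80%, and the effect detectable with 80% power is f of about 0.22, slightly below the conventional medium value of 0.25.

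The conclusion rests on the three sessions being the three groups, on all students attending all sessions, and on large meaning about f = 0.40. The size of the gap means that the third assumption is not critical. The point does not show that the study is underpowered or that recruitment should be cut. It warrants correction before results are reported, but does not threaten the conduct of the study.

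**What to change.** Keep 65 tandems and 130 participants, and revise the Sample Size Calculation as follows:

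1. Give f as a number.
2. State that 65 is the number of tandems per session, giving 195 team-sessions.
3. Restate the basis: 80% power at f of about 0.22, for one omnibus test of one score at alpha 5% (88% at f = 0.25).
4. Label these figures nominal, because the same students take part in all three sessions and independence is only an approximation.
5. If fewer tandems are achieved, report the detectable effect for the number completing all three sessions (for example, f of about 0.345 if 28 do so), instead of judging the trial against 65 for a large effect.

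The Abstract's enrolment figure can stay. The cost is a change of wording only, with no additional participants and no change to procedures.
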